#### 2.9.3. Secondary Outcomes

(1) Single Dyspepsia Symptom Scale (SDS)

The SDS questionnaire evaluates the frequency, intensity, and bothersomeness of the most common symptoms of FD, using a 4-point Likert scale, i.e., by measuring the following symptoms: postprandial fullness/bloating, early satiety, and epigastric pain and burning [11]. A higher sum of scores corresponding to the symptoms means more severe indigestion. SDS will be obtained at all visits except the screening visit and telephone follow-up (Visit 6). The degree of improvement in the SDS score will be calculated in the same way as that of the TDS.

(2) Overall Treatment Effect (OTE)

Using the OTE questionnaire, the subjectively perceived therapeutic effect on dyspeptic symptoms and quality of life will be assessed. At all visits after allocation, participants will be asked about how much their symptoms improved compared to before participating in the clinical trial, by answering with one of the following 7 items: “very much worse,” “much worse,” “slightly worse,” “no change,” “slightly improved,” “much improved,” and “very much improved” [12]. The response rate for each item will be calculated, and participants who responded “much improved” or “very much improved” will be defined as responders.

(3) VAS for Dyspepsia

Participants will check the intensity of dyspepsia symptoms over the past 2 weeks themselves using a VAS in a horizontal line drawn from 0 (not uncomfortable at all) to 100 (the worst dyspepsia you can imagine). The scores will be obtained at all visits except baseline (Visit 2) and telephone follow-up (Visit 6).

(4) FD-related Quality of Life (FD-QoL)

The FD-QoL is a questionnaire used to evaluate the quality of life of patients with FD, which consists of 21 items in four dimensions, including psychological, role-functioning, eating, and liveliness status. It has been validated for Korean patients with FD, where lower scores represent a worse quality of life [23]. Data will be collected at baseline (Visit 2), week 3 (Visit 3), and week 6 (Visit 4).

(5) HADS

The HADS questionnaire has a total of 14 items and consists of seven anxiety subscales and seven depression subscales. Each item is evaluated on a 4-point scale, and a higher score means more complaints of symptoms [24]. It will be measured at all visits except baseline (Visit 2) and telephone follow-up (Visit 6).

(6) Five-level Version of the EuroQol Five-dimensional Descriptive System (EQ-5D-5L)

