**Hypothesis** **1.**
*[*

$H_{0}\;:\;\mu_{1}=\mu_{2},\;H_{1}\;:\;\mu_{1}\neq \mu_{2}$

*]*

*-*

$\mu_{1}$

*: Change in TDS score of the YGJ group at week 6*

*-*

$\mu_{2}$

*: Change in TDS score of the usual care group at week 6*

A two-sided test with a significance level of 5% will be conducted using a mixed-effect model repeated measure (MMRM) with participants as the random factor and the treatment group and time of visit as the fixed factors. If necessary, analyses will be performed by setting variables showing statistically significant differences in demographic characteristics or variables that can affect dyspepsia as the fixed factors. The second purpose of this study is to evaluate the noninferiority of YGJ compared to that of PWS (Hypothesis 3). Consequently, the noninferiority margin (*M*) will first be defined based on the results of the effect evaluation of PWS compared to usual care at week 6 (Hypothesis 2), and the analysis method will be the same as that of Hypothesis 1.

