Other secondary outcome measures will be tested in the same way as the primary outcome measure. In addition, to compare the difference between the values before and after treatment in each group, the continuous variable will be analyzed using Student’s paired *t*-test or Wilcoxon signed-rank test, and the discrete variable will be Fisher’s exact test. Repeated measures analysis of variance will be performed to compare the differences in trend change in each group of visits, and Dunnett’s procedure (based on the baseline) will be used as a multiple comparison correction.

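### Section 2.11 names Fisher's exact test for paired before/after comparisons of discrete variables, where a paired test is needed; a smaller point is that the primary method does not suit the OTE responder endpoint

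*Protocol article*

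**What the plan says.** Section 2.11 (Statistical Analysis), in the paragraph after Hypothesis 3, sets out supplementary within-group tests. Their stated purpose is "to compare the difference between the values before and after treatment in each group". For continuous data, "the continuous variable will be analyzed using Student’s paired" *t*-test or the Wilcoxon signed-rank test. For discrete data, "the discrete variable will be Fisher’s exact test".

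The same paragraph opens with the general rule: "Other secondary outcome measures will be tested in the same way as the primary outcome measure". The primary method, set out under Hypothesis 1, is a mixed model for repeated measures (MMRM) "with participants as the random factor and the treatment group and time of visit as the fixed factors". The quantity compared is a change score: "Change in TDS score of the YGJ group at week 6" against the same change in usual care.

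Section 2.9.3 describes OTE as a seven-category rating collected only after allocation. Table 1 confirms this: it is marked at Visits 3 to 6 and not at Visit 2. Of its summary the section says "The response rate for each item will be calculated", and it defines responders as participants in the top two categories of improvement. Section 2.11 makes no exception for OTE.

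**The concern.** A before/after comparison within one group is a paired comparison. The two continuous-data tests in the sentence respect that; the discrete-data test does not. Fisher's exact test compares two independent samples or tests association in a two-way table, and neither is the question asked. A discrete variable of this kind can be formed from the plan's own measures: spleen qi deficiency yes/no, from the 43.18 cut-off on the Spleen Qi Deficiency Questionnaire (SQDQ), measured at weeks 0, 3 and 6. If the sentence is followed, the reported p-value will either be too large or answer a different question.

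For OTE, no change from baseline can be formed from the recorded values, and the endpoint that the protocol defines is binary. The Discussion names OTE, with the total symptom score, as a recommended primary endpoint for trials in this condition, so its between-group comparison should be clearly fixed.

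**Working it through.** **Inputs from the documents.** Section 2.10 gives a difference of 2.70, SD 3.65, two-sided 5% level (two-sided per section 2.11), 80% power, ratio 2:1, evaluable numbers 44 (YGJ, and also PWS) and 22 (usual care), and 20% dropout.

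**Plan's own figure.** Usual-care n = (1 + 1/2) × (1.960 + 0.842)² × (3.65/2.70)² = 1.5 × 7.85 × 1.827 = 21.5, rounded up to 22, with 44 for YGJ. Then 22/0.8 = 27.5, rounded up to 28, and 2 × 28 = 56. The plan's numbers reproduce, so 44 and 22 are the right sizes for the illustration.

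**A single table, n = 44 (invented counts).** 16 yes/yes, 12 yes/no, 2 no/yes, 14 no/no. The status was present in 28 before and 18 after.
- Exact McNemar uses the 14 participants who switched: p = 2 × (1 + 14 + 91)/2¹⁴ = 212/16384 = 0.013.
- Fisher on the stacked counts (28/16 against 18/26): p = 0.054.
- Fisher on the before-by-after table (16, 12 / 2, 14): p = 0.005, but for association.

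The third result is not evidence of change. Take a table with no net change: 20 yes/yes, 6 yes/no, 6 no/yes, 12 no/no. McNemar gives p = 1.0, yet Fisher on the cross-table gives p = 0.006.

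**Rejection rates.** Assumed, not in the documents: prevalence p₁ = 0.6 before; p₂ = 0.6 (no change) or 0.4 (change) after; within-person correlation ρ from 0 to 0.6. The cell probabilities follow from P(yes, yes) = p₁p₂ + ρ√[p₁(1 − p₁)p₂(1 − p₂)]. For example, at ρ = 0.5 with a true change: 0.24 + 0.5 × 0.24 = 0.36 yes/yes, 0.24 yes/no, 0.04 no/yes, 0.36 no/no. Summing the multinomial probability of every table with p < 0.05 gives, for n = 44:

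| ρ | Power, McNemar | Power, Fisher stacked | No change: McNemar rejects | No change: Fisher stacked rejects | No change: Fisher cross-table rejects |
|---|---|---|---|---|---|
| 0 | 37% | 36% | 2.9% | 2.9% | 3% |
| 0.3 | 51% | 34% | 2.7% | 0.9% | 42% |
| 0.5 | 66% | 31% | 2.3% | 0.2% | 89% |
| 0.6 | 79% | 29% | 2.0% | 0.1% | 98% |

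At n = 22 and ρ = 0.5, power is 25% (McNemar) against 9% (Fisher stacked), and the cross-table version rejects 53% of the time with no change.

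**OTE.** No arithmetic applies. Section 2.11 requires the primary method, whose hypotheses concern change in score. Section 2.9.3 and Table 1 give no Visit 2 value for OTE and define the endpoint as responder yes/no. The rule and the endpoint do not match.

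**The case against.** The best defence is one of reach. The within-group tests supplement the between-group model and do not establish a treatment effect. The SQDQ score can be tested as continuous, and section 2.11 itself uses the 43.18 cut-off only as a subgroup variable. OTE has no value before treatment, so the Fisher sentence cannot apply to it. All of this stands, and it keeps the point small. It does not make the named test right: the sentence says within group, before and after, so reading it as a between-group test is not open.

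The illustration can also be questioned. Its prevalences and correlations are assumptions, and at zero correlation stacked Fisher and McNemar hardly differ. At 22 participants neither test has useful power. The high cross-table rejection rates need someone to read an association test as a test of change; the stacked reading is conservative and creates no excess of false positives. These limits are accepted, which is why a range is shown. Repeated ratings on one person over six weeks are nevertheless unlikely to be uncorrelated.

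Two stronger inferences are tempting, and the documents do not support them.
- A reader might infer that a linear model cannot be fitted to OTE at all. OTE is itself a rating of change since before the trial, and a mixed model on the seven-point rating at post-allocation visits could be run. The mismatch is with the literal change score and with the binary responder endpoint.
- A reader might infer from "Repeated measures analysis of variance will be performed" that participants with a missing visit will be dropped, or that this merely repeats the MMRM. The protocol names neither a procedure nor complete-case handling, and it gives this analysis its own task: visit trends with Dunnett comparisons against baseline. No fault is shown there.

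**Conclusion.** The Fisher wording in section 2.11 is wrong as written. This is a stated method that does not fit the stated comparison, not a detail left to an analysis plan. Under the assumed prevalences and n = 44, the cost on stacked counts ranges from almost nothing at zero correlation to about 50 percentage points of power at correlation 0.6 (79% against 29%). The cross-table form does not test change at all.

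The OTE point holds in the smaller form: the assigned change-score model does not suit an outcome without a baseline value whose endpoint is responder status.

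A reader should not conclude that the discrete secondary outcomes in general, or the main results, are compromised. Hypotheses 1 to 3 and the sample size do not depend on either sentence. The correction should be made, but the trial's principal conclusions do not hang on it.

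**What to change.** 1. In the within-group sentence of section 2.11, replace Fisher's exact test with the exact McNemar test for binary variables. For more than two categories, use a marginal homogeneity test (Stuart-Maxwell), or the Wilcoxon signed-rank test where the categories are ordered.
2. Add an exception for OTE to the rule for secondary outcomes: compare responders between groups with a logistic model for repeated measures (GEE or mixed) containing group, visit and group-by-visit, and report the week-6 odds ratio or risk difference. If responder counts are too small for that model, a between-group Fisher's exact test at week 6 is a legitimate fallback, because the groups are independent.

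The cost is a few lines of analysis wording. No data, visits or participants are added. The change should be documented before the data are analysed, so that the tests are prespecified.

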### 2.12. Economic Evaluation

We will conduct an economic evaluation along with the RCT for effectiveness and safety. We will estimate the cost-effectiveness of YGJ compared with PWS or usual care from the health care system and societal perspective. Costs will consist of medical costs, nonmedical costs (transportation costs, time costs, and care costs), and costs associated with productivity loss using the Work Productivity and Activity Impairment Questionnaire: General Health V2.0, which is the most frequently used instrument for measuring productivity loss in Korea [30,31]. Cost data will be obtained from each participant using a separately developed cost questionnaire and institutional data at all visits except at the screening visit. However, if necessary, data from Statistics Korea can be used. Effectiveness data will be collected from the main RCT. Utility data will be collected from the main RCT using the EQ-5D-5L questionnaire, and quality-adjusted life years gained will be calculated using the area under the curve method [25]. We will investigate the cost and effectiveness data of TDS, OTE, and EQ-5D-5L for economic evaluation through telephone follow-up at week 24, even after the end of the 9-week clinical trial for effectiveness and safety evaluation of YGJ. These effectiveness, utility, and cost data will be used to calculate the incremental cost-effectiveness (cost–utility) ratio between the YGJ and the control groups at each visit. If necessary, we will perform a one-way sensitivity analysis on possible variables and present a tornado diagram, and also perform a probability sensitivity analysis using the distribution and representative values of the variables. In addition, subgroup analysis will be conducted according to the RCT subgroup analysis plan of the effectiveness outcome measures. Among the dropout criteria of the clinical trial for effectiveness evaluation, if the investigator judges that it is no longer possible for a participant to participate in the trial due to an adverse reaction or comorbid disease in the clinical trial process, participants will not be excluded from the data collection of the economic evaluation, and a telephone follow-up survey will be performed at week 24 with the consent of the participants. If we cannot observe the full yield cost and effectiveness outcomes of interventions during the 6 months clinical trial period, we will develop a decision-analytic model and conduct a long-term evaluation by secondary analysis.

### 2.13. Data Management and Monitoring

A web-based CRF iCReaT (Osong, Republic of Korea) will be used for data collection and verification, and will be managed by an independent data management team from the Korea Institute of Oriental Medicine (KIOM). It is only accessible to investigators who are directly involved in this clinical trial and have received the relevant education. Although data entry will be performed only once by the investigators in each trial institution, data quality will be managed using two verification processes for each clinical research associate (CRA) and data manager (DM) of KIOM.

For data monitoring, CRAs from KIOM, a supporting institution, will visit the trial institutions regularly to confirm and check compliance with the clinical trial protocol, appropriate and accurate data collection, participants’ informed consent, adverse events, and management of investigational products during the trial period. No interim analysis has been planned. The trial will be terminated after all the planned participants have been recruited, relevant data have been collected, and CRA and DM have checked and verified all the data. There are currently no planned audits.

### 2.14. Patient and Public Involvement

YGJ and PWS are herbal drugs approved by KMFDS in the Republic of Korea and have been used for the treatment of FD for many years. Hence, these medicines are easily accepted by patients. In particular, PWS is an herbal drug covered by health insurance benefits for patients with dyspepsia. We will use the patient’s subjective dyspeptic symptom intensity as the primary endpoint of our study, which is an important criterion in the clinical setting. However, patients were not involved directly in developing the trial protocol. Although there is no plan to communicate the study results to participants, we will provide a summary to the participants upon request after the completion of the clinical trial. Additionally, participants can contact investigators at any time to obtain information related to the clinical trial.

### 2.15. Ethics and Dissemination

The trial protocol has been approved by the IRBs of Kyung Hee University Korean Medicine Hospital (KOMCIRB 2021-01-001), Daejeon Korean Medicine Hospital of Daejeon University (DJDSKH-21-DR-03), and Semyung University Korean Medicine Hospital (SMJOH-2021-01). The protocol of this trial was registered at the Clinical Research Information Service (CRIS) (registration number: KCT0006044) before the enrollment of the first participant. Any modifications to the protocol will be reapproved by the IRBs and documented in CRIS. A detailed description of the trial process will be provided to participants by licensed Korean medicine doctors and, participants will be asked to sign an informed consent form prior to participation in the trial. The results of this study will be published in peer-reviewed journals and can be disseminated through conference presentations.

## 3. Discussion

The present study is a protocol for a randomized, assessor-blind, multicenter, controlled clinical trial evaluating the effectiveness and safety of YGJ compared with usual care and PWS in patients with FD, and will be conducted in conjunction with a cost-effectiveness analysis. We aim to test the superiority of YGJ to usual care and noninferiority to PWS for the treatment of FD. In addition, although YGJ is actively used in the Korean medicine clinical field for the treatment of FD, a cost-effectiveness analysis has not yet been conducted for this. We intend to prepare the basic data for health insurance benefit registration of YGJ by confirming the cost-effectiveness of YGJ compared to PWS, the most commonly used health insurance benefiting herbal medicine for the treatment of FD in Korean medicine clinical settings [7]. Based on consultation with Korean medicine gastroenterology experts and prior literature that stated that at least 4–6 weeks of treatment was required to see the significant therapeutic effect of YGJ, we set 6 weeks as the administration period of investigational products [12].

According to the guideline recommendations for outcome measures used in clinical trials for FD [32], the primary efficacy outcome measures to be used in FD clinical trials are diverse and have not yet been standardized. Additionally, in Korea, a patient-reported outcome measure that has been verified as recommended by local or global guidance has not yet been developed. Accordingly, it is recommended to use the total symptom score and OTE as the primary efficacy endpoint for FD clinical trials [32]. Therefore, in our study, the TDS score, which was used frequently as the primary outcome measure in previous studies on FD [11,19,22], was selected as the primary outcome according to the expert consensus, and OTE was set as the secondary outcome. Additionally, based on such previous studies [11,19], a sample size suitable for hypothesis testing was calculated in the present study.

In addition, based on previous studies showing that psychological factors are closely related to the pathogenesis of FD [12,33,34], we will measure HADS as a secondary outcome to determine whether anxiety and depressive symptoms are improved after administration of investigational products and to examine the correlation with other outcomes such as TDS and ghrelin.

According to the traditional Korean medicine theory, YGJ is a kind of herbal medicine that treats spleen qi deficiency and dampness-phlegm. We will also evaluate SQDQ and DQ as outcome measures to see if the symptoms of spleen qi deficiency and dampness-phlegm improve after 6 weeks of YGJ administration.

YGJ is a representative herbal medicine widely used in patients with FD. In recent years, experimental and clinical studies have been actively conducted to study the pharmacological actions of YGJ. In particular, various studies have been published showing that YGJ improves FD by enhancing ghrelin. However, due to the small number of specimens, no definite conclusion can be drawn [13,35]. Additionally, to the best of our knowledge, no studies have been conducted on the effect of PWS on ghrelin levels in improving FD symptoms. In addition to the self-reported subjective outcomes, we will measure changes in acyl-ghrelin, deacyl-ghrelin, and total ghrelin (acyl-ghrelin plus deacyl-ghrelin) levels before and after administration of the investigational products, which will also be used to explore different mechanisms of action for improving dyspepsia due to YGJ and PWS.

The YGJ and PWS which will be used in this clinical trial are approved by KMFDS. According to a previous study in which participants with FD were administered YGJ for 8 weeks [13], diarrhea (seven cases), nausea (three cases), headache (three cases), increase in the level of gamma-glutamyl transpeptidase (two cases), epigastric pain (two cases), increase in the level of alanine aminotransferase (one case), abdominal bloating (one case), abdominal discomfort (one case), common cold (one case), tinnitus (one case), skin abnormal sensation (one case), oral abnormal sensation (one case), vertigo (one case), and urticaria (one case) were reported as adverse events. There was no significant difference in the incidence of adverse reactions between the YGJ and the placebo groups, and no serious adverse reactions were reported in either group. In addition, in the previous study [17] in which modified PWS was administered for 8 weeks in participants with FD, no adverse reactions related to the PWS administration occurred. Therefore, we judged that the administration of YGJ or PWS for 6 weeks in this clinical trial is unlikely to cause serious harm to the participants.

One limitation of this study is that it is restricted to the Korean population, which may make the generalization of the results to other populations around the world difficult. However, the results of this study will prove the effectiveness and cost-effectiveness of YGJ, a non-covered herbal medicine for FD, in accordance with the national health insurance situation in Korea, thereby helping to expand the medical options and alleviate the health burden of Korean FD patients. The results of our study will provide strong evidence of YGJ, an important option for the treatment of FD, to clinicians, patients, researchers, and policy-makers.

## Figures and Tables

**Figure 1 healthcare-11-01456-f001:**
[figure not shown]
Flow chart of the trial process.

**Table 1 healthcare-11-01456-t001:** Schedule of enrolment, interventions, and assessments.

	Study Period					
	Enrolment	Allocation	Medication		Follow-Up	
Procedures	Visit 1 (Screening)	Visit 2	Visit 3	Visit 4	Visit 5	Visit 6 (Telephone)
TIMEPOINT	−2 weeks	Week 0	Week 3 ±4 days	Week 6 ±4 days	Week 9 ±4 days	Week 24 ±4 days
ENROLLMENT						
Eligibility screen	●					
Informed consent	●					
Demographics	●					
Medical and treatment history	●					
Physical examination	●					
Vital signs	●	●	●	●	●	
PIFD	●					
Allocation		●				
INTERVENTIONS						
YGJ or PWS		○	○	○		
Dietary guideline education		●	●	●		
ASSESSMENTS						
TDS		●	●	●	●	●
SDS		●	●	●	●	
OTE			●	●	●	●
VAS (dyspepsia)	●		●	●	●	
FD-QoL		●	●	●		
HADS	●		●	●	●	
EQ-5D-5L EQ-VAS		●	●	●	●	●
SQDQ		●	●	●		
DQ		●	●	●		
Cost questionnaire		●	●	●	●	●
Laboratory tests *	●			●		
Adverse events investigation		●	●	●	●	
Compliance test			○	○		

●: all participants, ○: YGJ and PWS groups, * Including hematological, blood glucose level, liver and renal function tests, electrolyte test, acyl-ghrelin, and deacyl-ghrelin. In addition, human chorionic gonadotropin urine test for women in their childbearing years, and anti-*Helicobacter pylori* serum IgG testing at the screening visit. Abbreviations. DQ, Damum questionnaire; EQ-VAS, the EuroQol visual analog scale; EQ-5D-5L, five-level version of the EuroQol five-dimensional descriptive system; FD-QoL, functional dyspepsia-related quality of life; HADS, hospital anxiety and depression scale; OTE, overall treatment effect; PIFD, pattern identification of functional dyspepsia; PWS, Pyeongwi-san; SDS, single dyspepsia symptom; SQDQ, spleen qi deficiency questionnaire; TDS, total dyspepsia symptom; VAS, visual analog scale; YGJ, Yukgunja-tang.

